**Fig. 2 Fig2:**
[figure not shown]
Screenshot of daily summary of travel behaviours in the TRavelVU app

##### Behaviour change program (the TRavelVU plus app)

The behaviour change program in the TRavelVU Plus app was developed by Trivector AB © and researchers with experience in behaviour change interventions (obesity, physical activity and transport). The intervention is grounded in Social Cognitive Theory [26] and Social-Ecological [27] principles. To improve the reporting of the content in behaviour change interventions the behaviour change technique taxonomy is recommended [28]. Thus, key behaviour change techniques known to promote physical activity behaviour are included in the app’s features and text messages (e.g., general information about physical activity and active transport, information regarding consequences, barrier identification, specific goal-setting strategies and functions, self-monitoring and feedback on performance) [28]. See Table 1 for theoretical domains, behaviour change techniques and examples of messages. We also considered recommendations from previous research regarding message linguistics (e.g., grammar, spelling, and positivity), dosage, length as well as timing of delivery [29, 30]. Thus, participants receive 4–6 messages per week that contain no more than 200 characters. The program consist of a core set of messages scheduled to be sent at fixed time points throughout the intervention that all participants receive. The messages include practical tips, general information and strategies for behaviour change. The messages can be accessed at any time throughout the intervention and are organised so that the content follow the study timeline. Thus, in the beginning of the intervention messages provide information about features within the app and strategies for goalsetting, and later on the messages focus on past successes and strategies for sustained behaviour changes. The goalsetting feature allows participants to set weekly individual goals for active transportation (i.e., walking and cycling). Feedback is provided in graphical format, where participants can follow their daily and weekly achievements and as a summary of all previous goals (see Fig. 3). During the week a coloured symbol (red, yellow, or green) guides the participants if their present achievement thus far in time spent in active transportation is enough to reach their goal or if greater efforts are needed. Additionally, at the end of each week a feedback message is sent out, which is tailored and varied according to participants’ goals and level of goal achievement in hours and minutes (i.e., ≥100%, ≥70, < 70% or no goal was set).

**Table 1 Tab1:** TDF’s and BCT’s used in the TRavelVU (control) and TRavelVU Plus (intervention) apps

TDF	BCT’s	Example of a message in the TRavelVU Plus app
Knowledge	Information about health consequences Instructions on how to perform the behaviour Provide information about the behaviour Information about antecedents	You do not need professional equipment to get started. Find your old bike, borrow one or buy one secondhand. Find out where you can park your bike at work and decide your start date!
Skills	Behavioural practice/rehearsal Habit formation Habit reversal Behaviour substitution	Do you commute using public transport? Why not get off at an earlier stop and walk the rest of the way?
Social/professional role and identity	Identification of self as a role model	Do you think someone close to you would benefit from being more physically active? Remember, you’re a role model for others! Be the first to change to a more active lifestyle!
Beliefs about capabilities/Optimism	Verbal persuasion to boost self-efficacy Mental rehearsal of successful behavior Focus on past success Verbal persuasion to boost self-efficacy	It is motivating to succeed in changing a habit. Start by setting a challenging but achievable goal, for example to cycle to work at least once a week instead of taking the car.
Beliefs about consequences	Information about social and environmental consequences Information about health consequences Pros and cons Comparative imagining of future outcomes Material reward (behaviour) Reward (outcome)	Cyclists contribute to cleaner air and less noise. Reduced car traffic makes the roads safer - safer roads promote cycling.
Reinforcement	Reward (outcome) Reward	Are there others in your household or at work who want to walk or cycle more? Set up a common goal to get started. Why not with a reward to do something fun together after you have walked or cycled 50 km?
Goals	Goal setting (behaviour) Problem solving Review behaviour goals Action planning Barrier identification Commitment	Is it possible for you to increase the time you spend walking and cycling? Set up achievable goals and check your progress (in the app) every day.
Intentions	Action planning Commitment	Is it difficult to get started with active transport? Plan your start date and stick to your plan, then take it one day at a time. Remember to set up achievable goals.
Social influences	Social support (practical) Social support (emotional) Social comparison Social support	Limited time is one reason why 50% of Swedish adults are physically inactive. Active transport can facilitate physical activity when there is no time for exercise. How can you create time for more active transport in your life?
Emotion	Reduce negative emotions Social support (emotional)	How are you doing? Changing habits can be challenging. Make sure to focus on what works.
Behavioural regulation	Self-monitoring of behaviour (outcome)^a^ Self-monitoring of outcome(s) of behaviour Feedback on behaviour^a^	Keeping track will help you to reach your goal. Go to *Summary* (in the app) to track your trips during the day and throughout the week. Is there any part of your travel that can be replaced with active transport?

The behaviour change taxonomy (v1) [28] where used to list theoretical domains frameworks (TDF’s) and behaviour change techniques (BCT’s) used in the TRavelVU and TRavelVU Plus apps

^a^Features present in the TRavelVU app availible to the control group (e.g., feedback as summary of active transportation (not in relation to a set goal))

**Fig. 3 Fig3:**
[figure not shown]
Screenshots of daily and weekly summaries of travel behaviours and achievements related to set goals

##### Pilot study

Prior to undertaking the full RCT a pilot study was conducted to assess the usability and content of TRavelVU Plus (features and messages) and to obtain other relevant information that could be integrated into the final version of the app. A convenience sample of 13 adults (7 women and 6 men, mean age 40 years) were recruited. The pilot participants were asked to use the app for two weeks and then complete questions regarding app usability, how they perceived the specific features in TRavelVU Plus, as well as the content and dose of the messages. Participants were also able to give general comments on the functions they did or did not appreciate, as well as to provide suggestions for improvements. As we were unable to test all messages via the app in the pilot study, semi-structured interviews were conducted via telephone with 8 of the pilot participants (3 woman and 5 men, mean age 36 years). During these interviews the entire message library (87 messages) were read aloud. Pilot participants were asked how they perceived each message and were encouraged to provide suggestions on how the message could be improved. The most appreciated features within the app were the goalsetting and self-monitoring functions. The battery consumption was reported as a limitation. Some participants thought it had been unclear how to edit trips and travel modes in the app. Another reported limitation was the inconvenience of having to specify all locations to be able to accept the registered day as valid. The messages were generally perceived as acceptable and relevant as well as delivered in a suitable dosage. However, more individually tailored messages were requested. Suggestions to add a step count function was also highlighted. Participants that were already physically active asked for more challenging messages and suggestions for exercise.

Based on the feedback from the pilot study, the app was revised. The updated app allows participants to accept a registered day as valid even if locations have not been specified (e.g., if one stopped to talk to a neighbour for 3 min during a longer walk). In regards to the manual the participants receive, we clarified how to edit trips manually and that greater battery consumption will occur when using the app. Furthermore, within the manual the study aim was highlighted (i.e., to increase physical activity through active transportation and not through exercise) so that the expectations of the study would be clear for the participants. After the pilot study and discussions within the research group minor changes were made to the wording of the messages and the number of messages were condensed from 87 to 61 to conform to the number needed during the intervention.

### Sample size and power considerations

A total of 200 participants (100 in each group) completing follow-up will provide 80% power (α = 0.05) to detect a 10 min difference in MVPA (e.g., 35 versus 45 min/day) assuming a standard deviation of 25 min [31]. Assuming about 20% drop-out rate between baseline and follow-up 250 participants will be enrolled in the study [32]. We will continue to sample until this goal has been reached. Based on our previous experience we estimate that 5000 randomly selected subjects will provide us with the sample requested when considering loss to follow-up and subgroup analyses [33].

### Outcomes and measures

The primary outcome is MVPA post intervention (i.e., 3 months post randomisation). Secondary outcomes include active transportation, neighbourhood walkability, health related quality of life and attitudes towards active transportation. Outcomes are assessed at baseline and at 3 and 6 months post randomisation. See Table 2 for an overview of all assessments. Unexpected and adverse events are voluntarily reported by participants to the research team and will be reported.

**Table 2 Tab2:** Outcomes and other measures collected at the different time points

		Baseline	3 months	6 months
*Assessments*	*Measure*			
MVPA, minutes/day	ActiGraph wGT3x-BT	x	x	x
Leisure and work time physical activity^a^	Questionnaire	x	x	x
Travel behaviour (active transportation)	Smartphone application (TRavelVU)	x	x	x
Health related quality of life	RAND-36	x	x	x
Attitudes towards active transportation	Transport and physical activity questionnaire (TPAQ)	x	x	x
Neighbourhood walkability	Neighbourhood environment walkability scale (NEWS)	x		
Sociodemographic factors^b^	Questionnaire	x		

Abbreviations: *MVPA* moderate-to-vigorous physical activity

^a^Two questions in the web-based questionnaire are used to assess leisure and work time physical activity [34]

^b^Occupational status, area of residency, type of housing and access to a bicycle were also repeated at the 3 and 6 month follow-ups

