### Participants and recruitment

Participants are recruited from a random sample of 5000 adults (aged 20–65 years) living in Stockholm County drawn from the population register at Statistics Sweden. Eligible participants are 20–65 years old, able to understand Swedish well enough to fully understand the study aims and consent to participate, and have access to a smartphone. Those who are unable to perform MVPA (i.e. brisk walking or cycling) will be excluded.

Potential participants are sent an inquiry letter by Statistics Sweden to their home address providing them with written information about the study. Participants register their interest via the study website, send in a response letter by post or contact the research group directly by email or telephone. Those who do not respond to the inquiry letter (including the two reminders after 2 and 4 weeks, respectively) will remain anonymous to the research team. Once informed consent is obtained, baseline measures are collected. Participants are asked to fill in a web-based questionnaire with questions regarding perceived neighbourhood walkability, attitudes towards active transportation, health related quality of life, self-reported physical activity level and socio-demographic data. Thereafter, participants are asked to wear an accelerometer to measure physical activity for seven consecutive days. Participants are also asked to download an app free of charge on to their smartphone, TRavelVU (Trivector AB ©), which passively captures travel behaviour for the same seven days as the accelerometer is worn. The app is compatible with both iOS (version 8.4 or higher) and Android (version 4.4 or higher) smartphones.

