### Randomisation and blinding

Upon completion of baseline measures, participants are randomised to the intervention or the control group in a 1:1 ratio. A computer-generated random allocation sequence list (in blocks of two) is generated in Stata 13 (StataCorp LP, College Station, Texas, USA). To ensure allocation concealment to study personnel until group allocation, the allocation list is monitored by a member of the research group with no participant contact. After randomisation, participants receive an email containing information about their group allocation. Assessors of the primary and secondary outcomes are blinded to group allocation; however, due to the design of the study participants are not blinded to their allocation.

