### Intervention

#### Overall

The overall aim of the SCAMPI intervention is to increase physical activity levels by promoting active transport. Once allocated to the intervention group, participants receive an email with a user manual for the TRavelVU Plus app. This app differs from the TRavelVU app as it includes a 3-month behaviour change program promoting active transportation. Features of the TRavelVU Plus app (i.e., messages (sent as push notifications), goal setting and feedback functions) are activated and start with a welcome message. The message includes a goalsetting function where participants set their first weekly goal for active transportation, for example 5 h. As guidance, they are informed of the recommendations for adults of 150 min of MVPA per week, but are encouraged to set a goal based on their current activity level. Feedback on the goal is provided in different formats during the week. At the end of the week, participants are able to adjust their goal for the following week. After 3 months, the features of TRavelVU Plus disappear; however, participants are encouraged to keep registering their travels in the TRavelVU app until after the 6-month follow-up assessment.

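### Adverse events are collected only when participants volunteer them, with no harm question at any scheduled assessment, so falls and traffic injuries will probably be under-counted and counts by arm may not be comparable

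*Protocol article*

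**What the plan says.** All references are to the Protocol article.

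- **Collection of harms** (Outcomes and measures): "Unexpected and adverse events are voluntarily reported by participants to the research team and will be reported". No other route is described: no solicited question, checklist, register linkage or safety contact.
- **Schedule** (same section): "Outcomes are assessed at baseline and at 3 and 6 months post randomisation", and "See Table 2 for an overview of all assessments". The rows of Table 2 are MVPA, leisure and work activity, travel behaviour, quality of life, attitudes, walkability and sociodemographic factors. None concerns injuries or adverse events. RAND-36 measures perceived health in eight domains and does not record events.
- **Questionnaire vehicle**: at baseline, "Participants are asked to fill in a web-based questionnaire" (Participants and recruitment). Table 2 and its first footnote show web-questionnaire items repeated at 3 and 6 months.
- **Blinding** (Randomisation and blinding): "Assessors of the primary and secondary outcomes are blinded to group allocation", but "due to the design of the study participants are not blinded to their allocation".
- **Contact by arm**: of the intervention app the article says "it includes a 3-month behaviour change program promoting active transportation" (Intervention, Overall), and under the behaviour change program "participants receive 4–6 messages per week that contain no more than 200 characters". Controls get no behaviour change content but use the monitoring app for 6 months (Control group).

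**The concern.** The programme asks people to walk and cycle more, and one sample message in Table 1 suggests finding, borrowing or buying a bicycle. Falls and traffic injuries are therefore the harms one would expect to look for. A participant who is never asked about an injury may not think to report it, so a volunteered count is likely to be too low.

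A second difficulty is conditional. Participants know their arm, and the arms differ in the content they receive. An intervention participant hurt while cycling may connect the injury with the study, whereas a control may not. Equally, someone loyal to the programme may keep quiet. Blinded outcome assessors cannot correct for an event that is never volunteered.

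What is at stake is how the events are interpreted. The article commits to reporting them, and its Discussion looks ahead to use by municipalities. A low volunteered count would not support a statement about safety.

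**Working it through.** **1. The plan's own figure.** The article gives no figure for adverse events. Its only sizing calculation is for MVPA (difference 10 min/day, SD 25, two-sided alpha 0.05, power 80%). It reproduces: 99 per arm by the normal approximation against 100 stated, with power 0.807 at 100 per arm. Enrolment is 200 / (1 − 0.20) = 250, or 125 per arm at 1:1. The point does not depend on this calculation; it supplies only the 125 and the 100 used below.

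**2. What volunteered reporting does to the counts.** Let p be the true risk in an arm and r the probability that an event is reported. Then

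- expected recorded events = 125 × p × r
- recorded risk ratio = true risk ratio × (r intervention / r control)

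Both p and r are assumptions. Take a control risk of 8%, so 125 × 0.08 = 10 true events.

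| True events (int. v control) | Reporting (int. v control) | Recorded | True ratio | Recorded ratio |
|---|---|---|---|---|
| 10 v 10 | 50% v 50% | 5 v 5 | 1.0 | 1.0 |
| 10 v 10 | 30% v 30% | 3 v 3 | 1.0 | 1.0 |
| 10 v 10 | 50% v 40% | 5 v 4 | 1.0 | 1.25 |
| 10 v 10 | 60% v 30% | 6 v 3 | 1.0 | 2.0 |
| 10 v 10 | 30% v 60% | 3 v 6 | 1.0 | 0.5 |
| 20 v 10 | 30% v 60% | 6 v 6 | 2.0 | 1.0 |

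Any reporting probability below 1 under-counts: 30% in both arms loses 14 of 20 events (70%), and 60% against 30% loses 11 of 20 (55%). The ratio is distorted only when reporting differs by arm, and it can move either way. The last row shows a real doubling hidden.

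**3. How much a count of this size could show.** Recorded events of 6/125 v 3/125 give a ratio of 2.0. The standard error of its logarithm is √(1/6 − 1/125 + 1/3 − 1/125) = 0.696, so the 95% interval is 2.0 × exp(±1.96 × 0.696), about 0.5 to 7.8. Fisher's exact p is 0.50.

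**4. Would complete capture settle the risk?** Power for two proportions is Φ[(d − 1.96 × SE0) / SE1], where d is the risk difference and SE0 and SE1 are its standard errors with pooled and separate risks. For 8% v 16% with 125 per arm, d = 0.08, SE0 = 0.0411 and SE1 = 0.0408, giving about 49%. For 8% v 12% it is about 18%. With 100 completers per arm the two figures fall to about 41% and 15%.

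**5. What the timetable allows.** Trial status has randomisation from September 2017 to April 2018, 3-month assessments complete by July 2018 and 6-month assessments by October 2018. The article appeared on 16 July 2018. By then, participants randomised before about mid-January 2018 had passed 6 months, and most or all of the others had passed 3 months.

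**The case against.** The strongest reply is that no comparison is at risk. The article says only that events will be reported; Statistical analyses contains no between-arm test of harms, and neither the aims nor the hypotheses claim safety. This stands. A reader might infer that the trial's safety comparison is biased, but the document plans none.

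A reader might also infer that the intervention arm will report more because it receives more messages. The document does not support that. Controls log and view their travel for 6 months and have the same follow-ups, so they are not out of contact. Differential reporting is possible, but it is neither shown nor predictable in direction.

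The remedy has limits too. Solicited answers are still self-report by unblinded participants, so recall may itself differ by arm. With about 125 per arm, even full capture would not settle injury risk. On the published timetable the remedy reaches many participants late or not at all. All of this stands.

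Finally, safety detail may sit in a fuller document that is not shown. That would be a good answer to silence, but here the article states the method, and the method is weak. None of these replies removes the likely under-count.

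**Conclusion.** The point holds in a limited form. Voluntary report is the only stated route, and the schedule contains no harm item, so falls and traffic injuries will probably be under-counted. This rests on spontaneous reporting being incomplete, which is very likely but cannot be quantified from the article. If reporting also differs by arm, counts by arm would not be comparable, with the direction unknown.

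The 8% risk and the reporting probabilities are assumed. Across the cases with no true difference, the recorded ratio runs from 0.5 to 2.0 and equals 1.0 whenever reporting is equal. The primary MVPA result is untouched. This is a cheap improvement to how harms are collected and described; it does not threaten the trial's main conclusion.

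**What to change.** - Add one or two closed questions, identical in both arms, to the existing 3- and 6-month web questionnaires: any fall, traffic accident or injury since the last assessment.
- Report the solicited events descriptively by arm and list volunteered events separately.
- Draw no conclusion on safety or relative risk from the volunteered count.
- Where the 3-month round is already complete, ask at 6 months with recall since randomisation. For participants past 6 months, label the data as volunteered only.

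**Cost.** One or two items in questionnaires already sent and a minor ethics notification, with no extra staff or visits. The downsides are slight participant burden, recall error that may differ by arm because participants are unblinded, partial capture of earlier entrants, and too few events for a firm risk comparison.

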#### Physical activity and MVPA

Leisure time and work related physical activity were measured with two questions included in the web based questionnaire [34]. To provide an objective assessment of physical activity an ActiGraph wGT3x-BT accelerometer (https://www.actigraphcorp.com/) are sent by mail to participants’ homes for them to wear for seven consecutive days. The accelerometer is worn on the waist at the mid-axillary line (on the right side), lying on the iliac crest during waking hours. The participants are asked to report all time points when the accelerometer was not worn in a diary accompanying the accelerometer (e.g., when taking a shower). The accelerometers are set to collect data at 90 Hz. The collected data will be processed in accordance with our previous procedures [35] following the accelerometer data processing criteria (e.g., regarding cut-points for MVPA, number of valid days) published in our recent review [36].

